#### fMRI Measurements (A, B, and C)

For the fMRI measurements, detailed manuals are provided to the researchers who conduct measurements. Furthermore, researchers are trained before they conduct parts of the study with participants. During fMRI measurements, two researchers are present. Protocols will be written for fMRI measurements.

#### Stimuli

In order to gain an advanced understanding in the engine of integration mechanisms and their neural correlates in patients with schizophrenia, participants undergo fMRI measurements watching videos on a screen^1^ before and after the actual training and waiting-list program (assessments A, B, and C). These videos differ from the ones presented in the familiarization session and from videos utilized during the MSG training procedure. The videos were recorded with an actor expressing concrete or abstract sentences (for an explanation of concreteness see “gestures in schizophrenia” in the background section). These sentences were recorded in three different modalities: accompanied by gesture (bimodal), without gesture (auditive modality) and gesture only/without speech (visual modality). The videos were standardized, extensively evaluated and had been successfully applied in a large number of fMRI (14–16, 84), EEG (85), tDCS (68, 86) and patient studies including patients with schizophrenia (30, 31). Altogether, we use six categories of videos in our study: videos containing.

concrete sentences accompanied by gesture (SG_CON)abstract sentences accompanied by gesture (SG_ABS)concrete sentences without gesture (S_CON)abstract sentences without gesture (S_ABS)concrete gesture without speech^2^ (G_CON)abstract gesture without speech (G_ABS)

Hence, there are three conditions of modality (bimodal, visual modality, auditive modality) and two conditions of concreteness (concrete and abstract) in our stimuli.

Videos of the n-back task comprise sentences with deictic content, containing pointing gestures. Again, these videos were recorded in three different modalities:accompanied by deictic gesture (bimodal: SG),without gesture (auditive modality: S),gesture only/without speech (visual modality: G).

These videos were standardized, extensively evaluated and had been successfully applied in a study (90).

To investigate repetition effects, the stimuli in the three fMRI measurements (A, B and C) are balanced: 50% of the videos are repeated at each assessment and 50% of the videos are completely new.

We developed eight different counterbalanced versions of stimuli presentation to avoid sequence effects.

#### Tasks

In a first task, the videos are presented to the participants who simply should confirm that they attentively watched (passive task). This allows us to compare the impact of concreteness and abstractness (due to concretism in schizophrenia) and different modalities [auditive vs. visual modality and the integration of both: cf. (15, 31)] on behavioral outcome and neural activation. In a second task, participants conduct an n-back task (one back and two back), where again different videos (speech, gesture and speech-gesture videos) are presented, but some of them are repeated directly (one back) or indirectly/with one new video in between [two back: see (61) for a review about a comparable approach].

#### fMRI Paradigm

The subjects are instructed to tap the fingers of their left hand on the buttons of a response box that is fixated at the subject's left leg. In the first task (passive task), subjects are asked to tap with their left forefinger to confirm that they watched the video (and to ensure they stay awake). In the second task (n-back task), participants are asked to tap with their left forefinger or their left middle finger, depending on their answer if the presented video seems to be a new or a repeated video.

Imaging data are collected with a 3 T whole body MRI system (SIEMENS MAGNETOM TrioTim syngo MR B17) equipped with a standard head coil. Structural image acquisition consists of 128 T1 weighted sagittal slices (slice thickness = 1.6 mm; FoV = 260 mm; TR = 3.15 s; TE = 1.37 s). To measure BOLD changes in brain activity during acquisition, T2* weighted gradient echo planar imaging (EPI) with 34 slices covering the whole brain will be used (voxel size = 3 x 3 x 4 mm; descending slice acquisition; slice thickness = 4.0 mm; TR = 1650 ms; TE = 25 ms; flip angle = 70°; FoV = 192 mm; GRAPPA = 2). Slices are adjusted after the anterior commissure posterior commissure (AC- PC) line. In the three measurements (A, B, and C), 936 functional images are acquired during acquisition phase in the passive perception task and 666 in the memory task (n-back task). A gradient echo field map sequence is measured before the functional runs to get information for unwarping B_0_ distortions.

Data will be analyzed using standard procedures of Statistical Parametric Mapping (SPM12 (91), RRID: SCR_007037) implemented in MATLAB R2018b (MATLAB (92), RRID: SCR_001622). Unwarping and realignment, slice time correction, coregistration, segmentation, and normalization to the standard space of the Montreal Neurological Institute brain (MNI-brain) as well as smoothing will be performed.

#### Multimodal Speech-Gesture Training: MSG Training

##### Examiners

The MSG training has been described in detailed manuals developed for the purposes of this study and are provided to the researchers who conduct the trainings. Speech language therapists, linguists, psychologists and medical PhD students with their focus on psychiatric disorders are involved in the training and are trained before they conduct parts of the study (e.g., the training) with participants. Examiners do not alternate between participants to ensure steadiness. During MSG training sessions, at least one examiner is present. Protocols are written during the trainings. Examiners were unaware about our specific neural and behavioral hypothesis regarding the MSG training effects on the different measures.

##### Setting

Trainings take place in an individual setting for reasons of acceptability by patients, taking into account that exercises including gesture performance are extraordinary and therefore possibly hard to execute when other participants are present. We offer eight sessions (60 min each) of training for reasons of a high drop out rate in trainings with more sessions in previous studies (93). These training sessions are offered with a high frequency (three to five trainings per week) as interventions in communication skills seem to be more efficient in high frequency interventions with short durations than in low frequency interventions with long durations in patients with schizophrenia (45). A higher frequency is not possible in our design because the training includes homework for reasons of transfer, offering the opportunity to do the homework exercises between two sessions.

##### MSG Training Procedure

Every session has a similar sequence of exercises, following best practice in therapy intervention. A session begins with small talk to establish a respectful relationship between participant and examiner and with a discussion about the homework prepared for the current session. Thereafter, participants should execute four exercises with increasing complexity (first two perceptual tasks, then a productive (imitation/mime) and a free productive (SG fluency) task. As in the fMRI measurements, video material is used where an actor produces sentences with a concrete or abstract meaning and accompanies these sentences with gesture. The videos differ from the stimuli in the fMRI measurements.

In the first perceptual task, the videos are presented through a laptop screen. Participants are supposed to rate the matching of gesture and speech content [see (68, 86)]. Considering the connection between speech/gesture perception and working memory (14, 21, 61), the second perceptual task is a speech-gesture-n-back task (one back, two back and three back with speech, gesture and speech + gesture videos).

In the first productive task, participants are asked to imitate the information in the videos presented to them or mime a given word/concept. In the second productive task, the SG fluency task, a semantic field is given to the participants (e.g., tools). In the style of verbal fluency tasks (94), participants have one minute to produce as many words as they can in this field of words and accompany these words by suitable gesture.

Considering the high impact of motivation on the positive outcomes of an intervention (95), participants are provided with some interesting background information about gesture and how it is related to language and communication (“what it is good for”) that is supposed to motivate them to attend to and talk about gestures in everyday life situations.

Handouts summarizing the content of this information and an explanation of the new homework are given to participants at the end of each session which hopefully allows them to transfer the training effects to their daily life routine.

#### Treatment as Usual: TAU

In addition to the fMRI before and after the training programme, we conducted a further fMRI measurement after a period of waiting (no training = treatment as usual: TAU). This will allow us to compare the outcomes from the training to a period of no training. This approach is similar to a training-TAU-design with two groups (one undergoing the training and a control group undergoing the treatment as usual, which means no training in our case).

### Outcome Measures and End Points

Our interest is the behavioral outcome of an MSG training on communication, social skills and quality of life as well as its neural correlates in brain regions.

Proposed behavioral outcomes are:

Behavioral data:Behavioral outcomes (n-back task performance: accuracy and reaction time for each condition) in interaction with treatment group (wait-training group vs. training-follow-up group) and time point (assessment A vs. B and B vs. C)Behavioral outcomes (n-back task performance: accuracy and reaction time for each condition) in interaction with subject group (patients vs. control group) and time point (assessment A vs. C)Behavioral improvement during training (speech-gesture matching and working memory performance: reaction time and percent correct, SG fluency performance: number of correct items and gesture imitation: experimenter evaluation of accuracy) as interaction with group (patients vs. control group) and time point (training session one to eight)Neural data:Neural activation (whole brain and specific regions of interest [ROI]: the left inferior frontal gyrus [IFG]) during the passive viewing and the n-back task in interaction with video condition, treatment group (wait-training group vs. training-follow-up group) and time point (Assessment A vs. B and B vs. C)Neural activation (whole brain and specific ROIs: STS and left IFG) during the passive viewing and the n-back task in interaction with video condition, subject group (patients vs. control group) and time point (Assessment A vs. C)Social data (self-report):Social functioning as measured by SASS – Soziale Aktivität Selbstbeurteilungs-Skala(87) in interaction with time point (*t_3_* vs. *t_5_*) and group (patients vs. control group)Quality of life as measured by SWLS – Satisfaction with Life Scale(89) in interaction with time point (*t_3_* vs. *t_5_*) and group (patients vs. control group)Communication skills as measured by a questionnaire for relatives of the patients (created for this study by our research team) in correlation with neural and behavioral measures of MSG related improvements (e.g., *t_3_* vs. *t_5_*)

In addition to that, we are planning to correlate the neural and behavioral outcomes as well as neural and social and behavioral and social outcomes.

For a summary/overview of the study see **Figure 2**.

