### Estimation and Appropriateness of Outcome

We expect to achieve a range of positive behavioural (73), neural (74, 75) and social outcomes (76).

We measure behavioral outcomes through the perception of videos with speech and gesture during fMRI measurements. We further expect that initial difficulties in memorizing gesture and speech information can be reduced due to the MSG training so that behavioral performance in a speech gesture working memory task (see below) is more similar to healthy controls after training. In addition to the outcome measures, we explore improvement over time during the eight training sessions regarding speech-gesture matching performance [reaction times (RT) and percent correct], gesture-speech working memory performance (RTs and percent correct), SG fluency performance (number of correct items) and gesture imitation (experimenter evaluation of accuracy) in dependency from speech content (concrete/abstract).

We measure neural patterns through fMRI during the perception of videos with speech and gesture information using specific experiments with iconic (concrete) and metaphoric (abstract) gesture materials (15) as well as an n-back working-memory task. Furthermore, we correlate the behavioral results with neural activation patterns using fMRI techniques before and after the training. Similar to the behavioral outcomes, we expect the neural activity of the patients in relevant brain regions [specifically the left posterior temporal lobe and the left inferior frontal gyrus, cf. (15, 30, 75, 77)] to converge to the neural activity of healthy controls.

As communication is the basis for social interaction and hence for quality of life, transfer effects will be investigated through standardized psychological questionnaires and a specifically outlined questionnaire about nonverbal communication and social life.

However, we do not yet know which exercises and measurements might be most appropriate in terms of acceptability of completion and variability of outcome. We are going to provide descriptive statistics.

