### Setting and Enrollment

#### Setting

This is a single-center randomized controlled trial of intensive single speech-gesture training versus wait-list control with a follow-up being conducted at Philipps-University Marburg, Department of Psychiatry and Psychotherapy. In this institution, 30 participants are recruited per subject group (30 patients with schizophrenia and 30 healthy controls). Outcomes are measured through pre-post-fMRI and standardized psychological questionnaires comparing two subject groups (patients with schizophrenia and healthy controls) and two intervention groups (wait-training group and training-follow-up group).

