**Figure 1 f1:**
[figure not shown]
Flow diagram of our study to assess the neural activation and behavioral outcomes of a speech-gesture training in patients with schizophrenia and a healthy control group. All in all, 60 people will participate in this study: 20 patients with schizophrenia in the wait–training group, 10 patients in the training–following-up group, 20 healthy controls in the wait–training group, and 10 controls in the training–follow-up group.

With this design, altogether, we will be able to compare 30 patients and 30 control subjects pre-to-post (assessment A vs. C, see **Figure 1**) with an equal number of repetitions (3 measurements each) as well as data from MSG training program of all subjects. In order to obtain sufficient data on specific training effects from MSG training (compared to TAU effects, repetition or general time effects in the waiting list group), we decided to include at least 20 participants per subject group (20 patients and 20 control subjects) in the wait-training group (wait-list control: without training between first and second measurement) and explore possible long-term effects in a small group of ten subjects per subject group (training-follow-up group: without training between second and third measurement).

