### Trial Status

The study started first fMRI measurements (assessment A) on 21^st^ December 2017 and after treatment as usual and the second fMRI measurement (assessment B), the training started on 20^th^ January 2018 with participants of the wait-training group. So far (end of March 2019), 18 patients and three healthy controls have been measured and completed the MSG training. With a sample of this size we cannot calculate any group differences yet. This will be done as soon as the samples are complete. After the first participants had completed measurements and training, we evaluated our design and the training make-up. By majority, participants were satisfied with the training and so far, we had only one dropout. Satisfaction can be shown through data from our standardized post training questionnaire, where 13 participants answered that the training was very satisfying, five answered that it was satisfying, no one of the patients who finished the training was unsatisfied with the training. Concerning transfer into everyday life social functioning, the training was rated as very relevant from five patients and as relevant from another five patients. Four patients where not sure, three patients rated the training as less relevant and one patient rated the training as not relevant at all. Regarding the ratings from the patients and considering the high rate of dropouts in other training studies involving patients with schizophrenia (93), we evaluated our design and training as feasible for this group of patients.

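### The randomised A-to-B contrast is set up as a group-by-time interaction, which wastes precision that adjusting for A would recover, and no A-to-B outcome is named as primary

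*Protocol article*

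**What the plan says.** All references are to the protocol article.

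- **Design.** Under Setting: "This is a single-center randomized controlled trial of intensive single speech-gesture training versus wait-list control". From A to B, one arm trains and the other waits. From B to C the wait-training arm trains and the other is followed up. A to B is therefore the only interval that compares training with waiting between randomised arms before both have been trained.
- **Allocation.** The Figure 1 legend gives "20 patients with schizophrenia in the wait–training group, 10 patients in the training–following-up group", and the same split for healthy controls. The imbalance is deliberate: "we decided to include at least 20 participants per subject group (20 patients and 20 control subjects) in the wait-training group".
- **Form of the contrast.** Outcome Measures and End Points lists "Behavioral outcomes (n-back task performance: accuracy and reaction time for each condition) in interaction with treatment group" and time point, with A against B and B against C as the time contrasts. Neural activation is treated the same way, with video condition as a further factor.
- **Ranking.** Behavioural, neural and social outcomes stand in one list. None is called primary.
- **Choice of measures.** Estimation and Appropriateness of Outcome says "we do not yet know which exercises and measurements might be most appropriate in terms of acceptability of completion and variability of outcome".
- **Progress.** Trial Status says "So far (end of March 2019), 18 patients and three healthy controls have been measured and completed the MSG training". It adds that group differences cannot yet be calculated and will wait for the complete samples.

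**The concern.** The form of the contrast costs precision. A change score gives the A value a fixed weight of one. Unless the A-to-B correlation is close to 1, that over-corrects for chance differences at A. Such differences are not small here: with 20 against 10, the standard error of the baseline difference is sqrt(1/20 + 1/10) = 0.39 SD.

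The missing ranking is the second problem. Several A-to-B tests have equal standing, and the text leaves the most suitable measures undecided while outcome data accumulate. A reader of the results could not tell whether a reported training effect was the one the trial set out to test.

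**Working it through.** **The plan's own figure.** 20 + 10 + 20 + 10 = 60, which agrees with the stated total. The article gives no alpha, power, effect size or SD, so the sample size cannot be re-derived. Below, two-sided 5%, 80% power and equal SD at A and B are assumed.

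**Interaction and change score.** On simulated data with 20 and 10 subjects and two time points, the repeated-measures interaction and the t-test on change gave the same result (t = 1.272, p = 0.214).

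**Precision.** Let rho be the within-arm correlation of A and B, in units of the baseline SD.

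- Variance of change: 2(1 − rho).
- Residual variance of B given A: 1 − rho².
- Large-sample ratio, adjusted to change: (1 − rho²) / [2(1 − rho)] = (1 + rho)/2.
- Cost of estimating the slope: 1 + 1/(N − 4), which at N = 30 is 1 + 1/26 = 1.0385.

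| rho (assumed) | (1 + rho)/2 | × 1.0385 | Variance reduction |
|---|---|---|---|
| 0.5 | 0.750 | 0.779 | 22% |
| 0.6 | 0.800 | 0.831 | 17% |
| 0.8 | 0.900 | 0.935 | 6.5%, about 7% |

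A simulation of 20 against 10 gave 22%, 17% and 6%, in agreement.

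**Detectable difference.** This is noncentrality × 0.387 × SD of the analysed variable. The noncentrality is 2.902 on 28 df for change and 2.906 on 27 df for the adjusted analysis, whose SD includes sqrt(1.0385).

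| rho | Change score | Adjusted for A |
|---|---|---|
| 0.5 | 1.12 SD | 0.99 SD |
| 0.6 | 1.01 SD | 0.92 SD |
| 0.8 | 0.71 SD | 0.69 SD |

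If healthy controls were pooled (40 against 20), the values at rho 0.5 would be 0.78 and 0.68 SD.

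**Number of tests.** The A-to-B arm contrast has 2 n-back measures × 3 modalities = 6, plus left IFG × 2 tasks = 2, so 8 in all. If independent, 1 − 0.95^8 = 0.337.

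The whole list depends on the counting rule:

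- **Condition as a factor:** n-back by arm 4, n-back A vs C 2, training sessions 6, ROI tests 8, SASS and SWLS 2. Total 22.
- **Conditions tested separately:** 12 + 6 + 6 + 8 + 2 = 34.
- **Also splitting by n-back load, with whole-brain maps and the relatives' questionnaire:** 24 + 12 + 6 + 8 + 6 + 3 = 59.

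Under the narrowest and widest of these rules the A-to-B subset is 4 and 16 tests, or 1 − 0.95^4 = 19% and 1 − 0.95^16 = 56%. Positive correlation between outcomes lowers all these figures.

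**The case against.** The article names no model and never speaks of a change score. The model may be fixed in an analysis plan that is not shown, and one constraining equal baselines would recover the precision. A group-by-time test in randomised arms is also valid and unbiased. All of this stands: the point concerns efficiency under the standard reading of the stated contrast, and the gain is slight if rho is high.

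The arm contrast is not expressly restricted to patients, so 20 against 10 is one reading of the sample. That stands too.

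A reader might infer that some 34 tests of equal rank make a false-positive training effect nearly certain (82.5% if independent). The documents do not support that. The count is one rule among several. The training-session measures are described as exploration in addition to the outcome measures; dropping those 6 leaves 28 tests and 76%. Most of the remaining tests are not the randomised A-to-B contrast.

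A reader might also infer that outcomes are being picked from the data. The sentence on measures speaks of acceptability as well as variability and is followed by a promise of descriptive statistics. Trial Status says that group differences had not been calculated. What remains is an opening for selection, with no sign that it has been used.

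**Conclusion.** The point holds as an advisable improvement on two counts.

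First, the stated A-to-B contrast in its standard form is less precise than a comparison of B adjusted for A. In patients alone the avoidable variance is about 22%, 17% and 7% at rho 0.5, 0.6 and 0.8. These sizes rest on assumed correlations, equal SDs at A and B, and the 20-against-10 reading.

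Second, no outcome is primary. The randomised contrast alone carries about 8 tests, and up to about 34% familywise error under independence. Since the article reports that no group differences have been calculated, a primary outcome can still be named credibly.

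**What to change.** 1. Analyse every A-to-B arm contrast with a linear model of the B score on arm and the A score, or with a longitudinal model constraining the arms to equal means at A. State whether patients are analysed alone or with controls.
2. Do not carry this adjustment over to the patient-versus-control contrasts. Those groups are not randomised and are expected to differ at A.
3. Before any between-arm data are tabulated, name one A-to-B outcome as primary and label the rest secondary or exploratory. The choice is the sponsor's; one n-back accuracy measure would be an example, but nothing in the article singles it out.

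The cost is about one paragraph and no new data. The downside is that the other outcomes lose confirmatory status.
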